E-mental health (e-mhealth) tools (i.e., the use of information technologies to deliver mental health services at a distance [18])—namely, web-based interventions (i.e., self-guided treatments delivered via websites and designed to educate and/or cause therapeutic change [19])—are an innovative form of intervention and seem to be a promising option to overcome most of the noted barriers, particularly given their many benefits: (1) improved access to care, since health care can become available regardless of time and place, contributing to health care equity and removing thresholds such as stigmatization; (2) empowerment, giving people the opportunity to take greater control of their own health care by enabling them to choose when and where they want to access it; (3) innovation, since these technologies open up a wide range of possibilities for health care and can provide the groundwork for sustainable changes; and (4) quality of care, owing to highly efficient and innovative systems and to effective interventions that lower costs and increase safety by reducing human errors [20]. These tools are already being used with adoptive parents in other countries [21,22]; however, none of them were specifically designed to help adoptive parents deal with the emotional challenges of parenthood or adopt mindful parenting practices; additionally, they are not prepared to be used in environments other than those for which they were designed—which makes their replication in the Portuguese context unfeasible. However, these interventions may offer valuable insights into features that should be considered in the development of a new intervention of this nature [23,24].

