### 2.2. Participants

The participants in Study 1 will be professionals who will have worked in Portuguese adoption services for at least 2 years.

In Studies 2, 3, and 4, the participants will be adoptive parents. To be eligible, parents will have to have (a) at least one adoptive child aged under 18 years; (b) no other adoption process in progress; (c) reading and writing abilities in the Portuguese language; and (d) regular access to the internet and electronic devices. In Studies 3 and 4, parents will be excluded if they will have been diagnosed with a serious mental health condition (e.g., schizophrenia).

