For Study 3, the e-mail will contain the link to the form with information about the objectives of the study. Through this link, respondents can express their interest in participating, provide their contact details, and provide permission to be contacted by the research team to schedule the session. The sessions will take place in person in a space belonging to the university that hosts the project. The participants will have access to a computer on which the intervention platform will be made available. They will be instructed to guide their own use of the platform—with the aim of bringing this experience closer to its real use—while simultaneously receiving an opportunity to express their thoughts about it. If needed, the participants will be prompted to keep talking during the session. Video and audio recordings will be made, and written notes will be taken throughout the sessions for later analysis. To augment the information obtained during this task with a quantitative aspect, participants will also be asked to complete a self-report questionnaire at the end of the session.

In Study 4, an e-mail will contain a link to a website where interested respondents can find detailed information about the project and the intervention and through which they can complete a request to be contacted by the research team. This contact phone call will be used to explain the study and the intervention in more detail, answer questions, and verify eligibility. After eligibility is confirmed, the participants will be randomized into two groups: an experimental group, with immediate access to *AdoptMindful2Care@Web*, and a control group, with access to the intervention only at the end of the study. In both groups, participants will have to complete online self-report questionnaires, the link to which will be sent via e-mail, at three different times: T0 (preintervention), T1 (postintervention; for participants in the experimental group, the link will be sent 2 days after completing the last module of the intervention, and for the waiting group, 8 weeks after completing the T0 step), T2 (1-month follow-up), and T3 (2-month follow-up).

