For Study 3, a minimum of 15 individual Think-Aloud Protocol sessions will be held with adoptive parents. Qualitative data will be analyzed by using thematic analysis [54] via the NVivo14© software program. All video and audio recordings of the sessions will be transcribed. On the basis of these transcripts and notes taken during the sessions, usability issues will be identified and rated according to their severity: minor, medium, or critical. Bugs will also be flagged and later reported to web developers. All usability issues rated as medium or critical will be coded on the basis of their content and subsequently mapped according to two predefined categories: navigation or functionality. After this categorization, the categories will be cross-referenced with the general “usability heuristics for users interface design” [55]. These heuristics are often used by experts in the field of user-experience design to inform design decisions, since they offer a set of valuable guidelines developed over decades for designing systems, identifying usability problems and creating better user experiences. The quantitative data will be analyzed via SPSS. Descriptive statistics will be used to explore the perceptions of adoptive parents regarding the prototype version of *AdoptMindful2Care@Web*.

In Study 4, 60 participants (30 per condition; 95% CI, power of 0.99, medium effects, repeated measures ANOVA, and within–between interaction; G*Power [53]) will be needed in the final evaluation. Owing to the expected dropout rate of 60% in e-health interventions [56], we will recruit a total of 96 participants. Statistical analyses will be conducted via IBM SPSS. Descriptive statistics will be used to evaluate the feasibility and acceptability of *Adoptmindful2Care@Web*. Repeated measures ANOVAs/linear mixed models (timeXgroup interaction) will be used to analyze the modifications in participants’ outcomes at the four different assessment times.

In Studies 1, 2, and 4, sociodemographic, clinical, and/or child-related variables will be controlled for in all statistical analyses, in order to account for possible differences between adoptive parents.

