## 5. Conclusions and Limitations

In summary, this study protocol outlines a comprehensive approach to developing a mindful parenting web-based postadoption intervention tailored to the specific needs of Portuguese adoptive parents. By incorporating user-centered design principles, namely, engaging fathers, mothers, and professionals throughout the process, we aim to create a tool that not only enhances the mental well-being of adoptive families but also addresses the systemic challenges they face in accessing appropriate care.

Despite the promising approach outlined in this protocol, it is important to recognize several limitations. 

Firstly, since this is a web-based intervention, some limitations associated with technology use may arise, particularly regarding accessibility. Participants may have varying levels of digital literacy, which could hinder their ability to engage fully with the intervention. To address this issue, we will design a user-friendly and intuitive platform, ensuring ease of navigation and understanding for all users. In addition, telephone calls will be made to assist with any difficulties that may arise in this regard. Moreover, we understand that *AdoptMindful2Care@Web* may lack the personalization and therapeutic alliance of the face-to-face version, which could affect user satisfaction and overall efficacy. To mitigate this obstacle, we will opt for formats that in some way approximate the experience of real contact, namely, videos recorded by psychologists and audio recordings, enabling participants to engage with relatable content that fosters a sense of connection. We will also collaborate with a company specialized in behavioral science that will help us adapt the contents of the intervention, making them more attractive and better engaging for participants while motivating their commitment to the program. Moreover, we are aware that privacy concerns and data security present ethical challenges in digital health platforms, as users may be apprehensive about the confidentiality of their information. In this regard, we will employ robust encryption protocols, maintain transparent privacy policies, and ensure compliance with relevant data protection regulations, such as GDPR. 

Furthermore, the focus on Portuguese adoptive parents may restrict the applicability of the findings to different cultural settings. 

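### Study 4 randomises individual parents with no household rule, so if both parents of a child enrol, about half of such couples would be split between website and waiting list

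*Protocol article*

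**What the plan says.** Section 2.2 of the protocol article defines the population parent by parent: "In Studies 2, 3, and 4, the participants will be adoptive parents". The first two criteria read "at least one adoptive child aged under 18 years; (b) no other adoption process in progress". The others concern reading and writing ability, internet access and, for Studies 3 and 4, serious mental illness. Both adoptive parents of one child can meet all of them.

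Section 2.4 (Procedure) has the agencies select potential participants and e-mail them. Interested respondents ask for contact, and a phone call checks eligibility. Then: "After eligibility is confirmed, the participants will be randomized into two groups". One group has immediate access and the other is "a control group, with access to the intervention only at the end of the study". Section 1 describes web-based interventions of this kind as "self-guided treatments delivered via websites and designed to educate and/or cause therapeutic change".

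Section 2.5 counts the sample in participants (60 analysed, 30 per condition). For the analysis, "Repeated measures ANOVAs/linear mixed models (timeXgroup interaction) will be used", with sociodemographic, clinical and/or child-related covariates and no household term. Table 1 lists parenting stress as a primary outcome, and mindful parenting and the child's difficulties as secondary outcomes. The child scales are hetero-reports, and parents are the only participants.

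**The concern.** Two parents of the same child share a home, a child and much of what the outcomes measure. If both enrol and are allocated separately, one may have the website while the other is meant to be untreated until the study ends. The programme runs on videos, audio and exercises at home, and its target is how parents respond to a shared child. The waiting-list partner can therefore be exposed directly, by watching along, or indirectly, through changes in the partner and child.

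Two things follow. The control arm is partly treated, so the estimated effect on parenting stress and mindful parenting is pulled toward zero. And in a split couple the same child contributes a rating to each arm, so any real change in that child appears on both sides of the comparison. Section 3 presents the pilot as preparation for a larger trial, and a diluted effect estimate would carry into its planning.

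**Working it through.** **Inputs from the article.** The unit allocated is the participant (2.4). There are two arms with 30 analysed per arm, power 0.99 and a medium effect (2.5). There are four assessments, T0 to T3 (2.4, Table 1). No household rule or term appears in 2.2, 2.4 or 2.5.

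**Assumed, because the documents give no figure.** p is the share of participants whose co-parent is also enrolled. c is the share of the effect that reaches a waiting-list partner. ICC is the within-couple correlation. Medium is read as f = 0.25, the 95% CI as two-sided alpha 0.05, with a correlation of 0.5 between repeated measures.

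**1. The plan's own figure.** For the within-between interaction, λ = f² × N × m / (1 − ρ), where m is the number of assessments and ρ the correlation between them. The degrees of freedom are (m − 1) and (N − 2)(m − 1).
- m = 3, N = 60: λ = 0.0625 × 60 × 3 / 0.5 = 22.5, power 0.991.
- m = 4, N = 60: λ = 0.0625 × 60 × 4 / 0.5 = 30, power 0.998. Here N = 50 already gives 0.99.

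So 60 reproduces as a calculation on independent participants.

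**2. How often a couple is split.** Under independent 1:1 allocation the chance is about 1/2 per couple. The chance of at least one split among k couples is 1 − 0.5^k: 87.5% for 3 couples, 97% for 5 and 99.9% for 10.

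**3. Dilution.** About p/2 of the waiting-list participants have a partner with access, and each receives a share c of the effect. The between-arm difference therefore shrinks by p/2 × c.

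| p | c = 0.5 | c = 1 (upper bound) |
|---|---|---|
| 0.3 | 0.15 × 0.5 = 7.5% | 15% |
| 0.5 | 0.25 × 0.5 = 12.5% | 25% |
| 0.8 | 0.40 × 0.5 = 20% | 40% |

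The right-hand column is closest to the child outcome, where both partners rate one child. It remains an upper bound, because two raters may differ.

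**4. Power at N = 60, m = 4**, with f multiplied by (1 − p/2 × c):
- p = 0.25, c = 0.25: f = 0.242, power 0.997.
- p = 0.5, c = 0.5: f = 0.219, power 0.987.
- p = 1, c = 1: f = 0.125, power 0.61.

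Power is robust except at the extreme. The problem is bias in the estimate.

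**5. Standard errors under individual allocation.** A same-arm couple adds covariance to the variance of the between-arm difference, and a split couple subtracts it. With about half of each, the terms roughly cancel: p × ICC × (1/2 − 1/2) = 0.

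**6. If couples are kept in one arm.** The design effect is 1 + p × ICC. For p = 0.3 with ICC = 0.3 it is 1.09; for p = 0.8 with ICC = 0.5 it is 1.40. Sixty parents then carry the information of 60/1.09 = 55 to 60/1.40 = 43. Matching 60 independent parents would need 60 × 1.09 = 65.4 (66) to 60 × 1.40 = 84.

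**The case against.** The strongest reply is that the article never says both parents of a child may enter Study 4. The sentence on randomisation would read the same if only one parent per family were taken, or if couples were allocated together. A condensed article may leave that to the full protocol, and agency selection and the phone call are places where such a rule could operate. The phrase "engaging fathers, mothers, and professionals throughout the process" in section 5 describes the four-study project, so it does not show co-enrolment in the trial. Every magnitude rests on assumed values, and in the middle case power is 0.987 against the stated 0.99. This is also a pilot, and section 3 lists randomisation procedures among the things it should help to optimise.

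Most of this stands, and it limits the point to a conditional one. A reader might infer that the article prescribes separate allocation of co-parents. It does not; it only leaves that open. What survives is that the published rules, followed as written, admit both parents and allocate participants. The bias toward zero does not depend on power.

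A reader might also infer that the standard errors are wrong and the type I error inflated, to roughly 6% to 10%. Those figures come from 2 × (1 − Φ(1.96/√DE)) at design effects (DE) of 1.09 and 1.40. They apply only if couples share an arm and their correlation is then ignored. Under individual allocation the two kinds of couple roughly cancel (step 5), so the documents do not support that claim.

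**Conclusion.** The point holds in conditional form. If co-parents enrol, the allocation as described would split about half of the couples, expose waiting-list partners at home, bias the between-arm effect toward zero and let one child be rated in both arms. With p = 0.3 to 0.8 and half the effect spilling over, the attenuation is about 8% to 20%; 15% to 40% is the ceiling under full sharing. None of p, c or ICC is in the documents, and if no couples enrol the loss is nil. No inflation of type I error is claimed for the present allocation. This is a cheap improvement to the procedure; it does not invalidate the trial.

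**What to change.** At the eligibility phone call already described in section 2.4, and before allocation, establish whether a co-parent will also take part. Then state one of two rules.

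- **One parent per household counts as the trial participant.** N stays at 60 and the analysis is unchanged. The cost is a slightly narrower recruitment pool.
- **The household is allocated as one unit after both parents have consented.** Use the linear mixed model that section 2.5 already lists, with a household random intercept, since the repeated measures ANOVA alternative cannot carry one. Name one reporting parent per child for the child scales. The cost is the effective sample size in step 6. Under the step 1 assumptions with four assessments there is some slack: at p = 0.5 and ICC = 0.3 the design effect is 1.15, the effective number is 60/1.15 = 52, and power is 0.994.

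Under either rule, a co-parent should not join as a participant once the household's arm is known, because that breaks allocation concealment and invites enrolment that differs by arm. The change is about a line in the procedure, plus one random effect and the reporting-parent rule under the second option.

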## 2. Materials and Methods

### 2.1. Design

*AdoptMindful2Care@Web* will be developed following the CeHRes Roadmap and by adapting the structure of its standard version (*AdoptMindful2Care*; [29]) according to the results of the current protocol.

*AdoptMindful2Care* is an eight-session, face-to-face group intervention in which adoptive parents learn to apply mindfulness and self-compassion skills to themselves and to their parenting experience. This intervention was built on the basis of the Mindful Parenting Program manual [13]. The following topics are covered: (1) automatic pilot parenting, (2) beginner’s mind parenting, (3) reconnecting with our body as a parent, (4) responding versus reacting to parenting stress, (5) parenting patterns and schemas, (6) conflict and parenting, (7) love and limits, and (8) a mindful path through parenting.

In *AdoptMindful2Care@Web*, we intend to keep the same content (each topic will correspond to a module), adapting its presentation format (e.g., through videos recorded by psychologists, audios, interactive texts, and interactive exercises) according to the results obtained in the exploratory studies we will conduct at the beginning of the project (Studies 1 and 2).

The CeHRes Roadmap [11] provides an evidence-based development approach for e-health interventions. It states that the development of an e-health intervention must incorporate the contributions of prospective users and other stakeholders throughout the entire creation and pre-testing process, which includes the contextual inquiry, value specification, and design phases. By creating a good fit among the human, technological, and contextual factors, this holistic approach can increase the degree to which an intervention reaches its goals. The development of *AdoptMindful2Care@Web* will be guided by a user-centered approach, which will rely on the active participation of adoptive parents—as its future users—and professionals working in adoption teams—as expected mediators of access to the intervention—through the entire process (Figure A1).

To achieve this goal, the present study protocol will be divided into three phases:
Phase I, which will be dedicated to contextual inquiry and value specification tasks. In turn, this phase is divided into two distinct but complementary studies:

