			**Parents with children > 2 years old** **Interpersonal Mindfulness in Parenting Scale** [IM-P [41]; PV: [43]): self-report measure; 31 items divided into 5 dimensions; Likert scale (ranging from 1 = never to 5 = always); higher scores indicate higher levels of mindful parenting.
	**E-health literacy**	**Portuguese version of the E-Health Literacy Scale** [44]: Self-report measure; 8 items; Likert scale (ranging from 1 = strongly disagree to 5 = strongly agree). Higher scores indicate higher levels of e-health literacy.	
	**Preferences and acceptability of an e-health intervention**	**Self-report datasheet, specifically developed by the research team, which will collect the information regarding the characteristics required of *AdoptMindful2Care@Web* to meet the adoptive parents’ acceptability and preferences regarding the intervention:** 22 questions with multiple-choice exclusive answer, multiple-choice questions with several possible answers, 5-point Likert scale, and yes-no answers; e.g., whether they would find it useful, whether they would be interested in participating, and preferences for content formats.	
**3** Adoptive parents	**Usability of *AdoptMindful2Care@Web***	**The Think-Aloud Protocol** will be used to examine how adoptive parents experience *AdoptMindful2Care@Web* in the context of its actual use. **A self-report datasheet**, specifically developed by the research team, will be used to collect quantitative data regarding the prototype version of *AdoptMindful2Care@Web* (e.g., how appealing and intuitive adoptive parents find the platform).	
**4** Adoptive parents	**Acceptability of *AdoptMindful2Care@Web***	**Self-report datasheet, specifically developed by the project team, which will collect information regarding the satisfaction with the contents and characteristics of the intervention and the opinions regarding the intervention’s quality and relevance:** 25 questions; Likert scale and multiple-choice exclusive answer; e.g., whether taking part in the intervention was useful, whether it helped to improve their relationship with their child, whether they would recommend the intervention to family or friends, whether they consider the technological resources provided by the platform to be adequate, the importance attributed to the different contents covered, and the usefulness attributed to the different technological tools provided.	

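### Study 4 sends the T1 questionnaire on programme completion in the web arm but at 8 weeks in the control arm, with no fallback for web-arm parents who do not finish

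*Protocol article*

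**What the plan says.** The rule is in the protocol article, section 2.4 (Procedure), in the paragraph on Study 4. Both groups are to complete online questionnaires sent by e-mail link. The T1 link depends on the arm: "the link will be sent 2 days after completing the last module of the intervention, and for the waiting group, 8 weeks after". The first clause is the web-arm rule. The second is the control rule, and its 8 weeks run from T0.

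The later assessments are given only as "T2 (1-month follow-up), and T3 (2-month follow-up"), with no stated starting point and no separate trigger for non-finishers.

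Other relevant statements:

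- Section 2.1 plans eight topics and says "we intend to keep the same content (each topic will correspond to a module"). It gives no pacing and no maximum duration.
- The Introduction describes web-based interventions in general as "self-guided treatments delivered via websites and designed to educate and/or cause therapeutic change".
- Section 2.5 plans repeated measures ANOVAs or linear mixed models with a time-by-group interaction over four assessments. It needs 60 participants (30 per condition) in the final evaluation and recruits 96, with the reason "Owing to the expected dropout rate of 60% in e-health interventions".
- Table 1 lists adherence, dropout and web-system data as feasibility measures. It names parenting stress and positive mental health as primary outcomes, evaluated at T0 to T3.
- The only reminder e-mails described, in section 2.4, are for the surveys of Studies 1 and 2.

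**The concern.** One trigger is something the participant does after randomisation. The other is a calendar date. Two consequences follow.

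**Selection.** A web-arm parent is asked for post-baseline outcomes only after finishing the programme. Every control is asked. The efficacy contrast then compares a self-selected part of one arm with the whole of the other, and randomisation no longer protects it. Parents who finish may differ from those who stop in motivation, stress or available time, and these could affect the primary outcomes whatever the intervention does.

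**Timing.** Control T1 falls 8 weeks after T0. Web-arm T1 falls whenever the parent finishes, plus 2 days. Any drift in parenting stress or mental health with time since T0 is then partly mixed with arm.

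The trigger also ties two feasibility questions together. Stopping the programme produces questionnaire loss by construction, so the pilot could not tell how willing non-finishers are to supply follow-up data. A later, larger trial would need to know that.

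**Working it through.** **1. Who is sent T1 under the printed rule**

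| | Web arm | Control arm |
|---|---|---|
| Trigger | last module completed + 2 days | T0 + 8 weeks |
| Finishes the programme | link sent | not applicable |
| Does not finish | no link stated | not applicable |
| Sent T1 | finishers only | all |

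The starting point of T2 and T3 is not stated. Counted from T0, a control's 1-month follow-up would come before the 8-week T1, so counting from T1 is the natural reading. If so, the loss carries through to T2 and T3.

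**2. Timing.** T1 coincides in the two arms only if the web-arm parent finishes on day 56 − 2 = 54. As an illustration, finishing on day 28 gives T1 on day 30, which is 26 days before the control T1. Finishing on day 84 gives day 86, which is 30 days after it.

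**3. Range for the completing share**

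- The plan's recruitment figure reproduces as 60 × 1.6 = 96. With 30 per condition in the final evaluation I assume equal allocation, so 96 / 2 = 48 per arm.
- Upper value: the plan's own retention, 30 / 48 = 62.5%.
- Lower value: the quoted 60% dropout read as non-completion, 48 × 0.4 = 19.2, about 19 web-arm parents.
- These two values disagree because 60% dropout applied to 96 leaves 96 × 0.4 = 38.4, not 60. That is a separate matter. Here the two values only bound the illustration.

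**4. Spurious difference with no true effect.** Let p be the completing share and r the correlation between a latent normal propensity to complete and the T1 outcome. The completers' mean is shifted by

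bias (in SD) = r × φ(z) / p, where z is the (1 − p) normal quantile.

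- p = 0.40: φ(0.2533) / 0.40 = 0.3863 / 0.40 = 0.966
- p = 0.625: φ(−0.3186) / 0.625 = 0.3792 / 0.625 = 0.607

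**5. False-positive rate.** For a two-sided 5% comparison of T1 means, SE = √(1/n + 1/48) SD, where n is the number of web-arm completers and all 48 controls are taken to respond. The rejection rate is Φ(−1.96 + bias/SE) + Φ(−1.96 − bias/SE).

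| p | n | SE | r | bias (SD) | rejection rate |
|---|---|---|---|---|---|
| 0.40 | 19 | 0.271 | 0.1 | 0.10 | 6% |
| 0.40 | 19 | 0.271 | 0.3 | 0.29 | 19% |
| 0.625 | 30 | 0.233 | 0.1 | 0.06 | 6% |
| 0.625 | 30 | 0.233 | 0.3 | 0.18 | 12% |

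**6. With T0 in the model.** Assume a T0–T1 correlation of 0.5 and r = 0.3 at both times. The bias becomes (0.3 − 0.5 × 0.3) × 0.966 = 0.145 SD at p = 0.40 and 0.15 × 0.607 = 0.09 SD at p = 0.625. The SE shrinks by √(1 − 0.25), to 0.235 and 0.202, and the rejection rates are about 9% and 7%. In an analysis of change from T0, the bias is zero if completion relates equally to T0 and T1.

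The values of r and the T0–T1 correlation are assumptions. The documents give neither.

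**The case against.** The strongest reply is that this is a condensed article about a pilot. The paragraph says that both groups complete the questionnaires, so the T1 wording may describe only the normal path, with a cut-off date for non-finishers held in a fuller protocol. Assessing parents after they finish also answers a legitimate question about the delivered programme. This lowers the certainty about what will happen in practice. It does not remove the point, because the article states a trigger for each arm and the two differ. If a fallback exists, the printed sentence still needs it. Preliminary efficacy is also a stated aim with named primary outcomes.

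A reader might infer more than the documents support:

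- *Web-arm dropouts are never assessed.* T0 is collected, and dropout and web-system data are recorded. What is missing is the post-baseline questionnaire.
- *No analysis can recover them.* A linear mixed model, which the plan names, can use their T0 values and is valid if data are missing at random given what was observed. With no post-baseline data from any non-finisher, that assumption cannot be tested.
- *The platform is self-paced, so timing will differ widely.* Self-guided is used of web interventions in general and does not mean unlimited pace. Eight modules and an 8-week control T1 are compatible with roughly weekly modules. Misalignment is possible, not shown.
- *Acceptability ratings will come only from finishers.* Table 1 describes a form on "satisfaction with the contents and characteristics of the intervention" but does not say when or to whom it is sent.
- *The 60% dropout is all web-arm non-completion.* Section 2.5 gives a single rate and does not define it that way.

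**Conclusion.** The concern holds as a defect in a stated rule. As printed, web-arm post-baseline data depend on finishing the programme, control data do not, and time since T0 can differ between arms. The time-by-group comparison is therefore open to selection bias that randomisation does not prevent.

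The size is uncertain. The unadjusted range of about 0.06 to 0.29 SD, with false-positive rates of about 6% to 19%, rests on 48 per arm, 40% to 62.5% completing, an assumed r of 0.1 to 0.3, and a response from every invited control. The upper end is a worst case from a raw T1 comparison and should not be read as the expected error of the planned analysis. That analysis includes T0, which reduces the bias and under one condition removes it. What does not depend on these assumptions is that the rule, as written, never requests the outcomes of web-arm non-finishers.

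**What to change.** In section 2.4 of the protocol article, and in the e-mail system before Study 4 starts:

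- Send the T1 link to every randomised participant in both arms at the same fixed time from T0, for example the 8 weeks already used for controls, whatever modules have been completed.
- Count T2 and T3 from that same date in both arms, and say so.
- Record whether and when the last module was completed as an adherence variable. A completer analysis can then be reported as secondary.

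The cost is one revised sentence and one changed e-mail trigger. The small downside is that some slow users will answer T1 before finishing the programme. The completion date will show who they are. The change has to come before the first T1 date, because outcomes not requested at the time cannot be collected afterwards.
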